## **2. Research Design and Methods**

### **2.1 Overall design**

This study is a parallel, randomized, multicenter clinical trial with 800 participants in 5 hospitals in China with 12-months follow-up. Eligible participants with uncontrolled type 2 diabetes will be randomly assigned to the mobile messaging-based intervention or usual care for 12 months. The primary outcome comprised the mean changes in HbA1c levels, LDL-C levels, and systolic blood pressure (SBP) levels from baseline to 12

51 months simultaneously modeled for a single overall treatment effect.

[figure not shown]

52 Figure 1. study design

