## 53 2.2 Randomization and masking

54 Eligible participants were randomly assigned to either the mobile messaging-based intervention or control  
55 group in a 1:1 ratio. Randomization was stratified by study centers and performed centrally at the Research and  
56 Data Coordinating Center in Nanfang Hospital. The randomization schedules were generated using the PROC  
57 PLAN procedure in SAS statistical Software with a block size of six (Version 9.4). The research nurses,  
58 investigators, and statisticians were blinded to the treatment allocation. The clinical outcomes were also  
59 collected by blinded research doctors during the study period.

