#### **5.2.1 Data analysis plan**

Data was analyzed according to participants' randomization assignments, regardless of their subsequent status (intention to-treat principle). All the analyses will be conducted using SAS version 9.4 (SAS Institute Inc). Group differences in the trial outcomes will be evaluated using the general linear model for continuous variables and the chi-square test for categorical variables. Continuous variables will be presented as mean  $\pm$  standard deviation (SD) or median (interquartile range), and categorical variables will be presented as frequencies with percentages. In this study, the overall intervention effect on HbA1c, LDL-C, and SBP will be tested using a scaled marginal model, in which each outcome was scaled by its SD. Generalized estimating equations will be used to calculate the regression coefficient and outcome-specific scale variables in SAS PROC GENMOD, and the assumption of an overall intervention effect will be tested using a score test(30). Group differences for the secondary outcomes will be also evaluated with the use of the generalized estimating equations for continuous variables adjusting for baseline levels corresponding to each study outcome. In addition, the correlations of outcomes among participants within each clinic center using an exchangeable

correlation structure will be also taken into account in the analysis. Multiple imputations for missing data in the multivariable analyses will be conducted using the Markov chain Monte Carlo method.

Subgroup analyses of HbA1c, LDL-C, and SBP will be also conducted according to age ( $\leq 60$  and  $> 60$  years), sex (male and female), education levels (junior high school degree or below, high school education or above), employment status (never worked/unemployed, retired and on duty), smoking status (never, former and current), current drinking (yes or no), prevalent obesity (yes or no), prevalent hypertension (yes or no), prevalent hypercholesterolemia (yes or no). A two-sided P value less than 0.05 is considered statistically significant.

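### The exchangeable within-centre correlation makes the 5 hospitals the GEE clusters, too few for an uncorrected sandwich variance; the clustering unit should be the participant, with centre as a fixed effect

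*Protocol*

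**What the plan says.** Section 2.1 describes a "multicenter clinical trial with 800 participants in 5 hospitals in China". Section 2.2 has individual participants allocated 1:1, and "Randomization was stratified by study centers and performed centrally", so both arms are present in each hospital.

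Section 5.2.1 then sets out, in this order:

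- **Primary.** The joint effect on HbA1c, LDL-C and SBP "will be tested using a scaled marginal model, in which each outcome was scaled by its SD", fitted by GEE in PROC GENMOD, and "the assumption of an overall intervention effect will be tested using a score test".
- **Secondary.** "Group differences for the secondary outcomes will be also evaluated with the use of the generalized estimating equations for continuous variables", with adjustment for baseline.
- **Centre.** A further sentence brings in "the correlations of outcomes among participants within each clinic center using an exchangeable" structure. Its reach is stated only in general terms: this "correlation structure will be also taken into account in the analysis".

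The section names no variance estimator (empirical or model-based), no small-sample correction and no degrees of freedom for the score test. Significance is judged at two-sided 0.05.

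**The concern.** A working correlation among participants of the same centre means that the centre is the GEE cluster. The empirical variance of GEE is a large-sample result in the number of clusters, and here there are five, however many patients each contains. Centre is also not the unit of randomisation. It is a stratum, and the treatment comparison can be made within it, so nothing in the design calls for centre to be the independent unit.

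For the primary model there is a second difficulty. The three stacked outcomes are correlated because they come from the same patient. A single exchangeable structure at centre level gives two outcomes of one patient the same correlation as outcomes of two different patients, so it does not represent the dependence that the scaled marginal model has to handle.

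At stake are the p-values and confidence intervals of the continuous secondary outcomes and, on the wider reading, of the primary test.

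**Working it through.** **Figure to compare with.** The plan states no operating characteristics for the GEE analysis. The only benchmark is its nominal two-sided 0.05.

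**Inputs from the protocol.** K = 5 centres (section 2.1). 400 per group with 20% dropout (section 5.1) leaves 400 × 0.80 = 320 per group, 640 in all. The stated differences in SD units (section 5.1) are 0.5/1.6 = 0.31 for HbA1c, 5/18 = 0.28 for SBP and 0.25/0.96 = 0.26 for LDL-C.

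**Assumptions, not in the protocol.** Uncorrected sandwich variance, centre sizes, intra-centre correlation (ICC), correlation between outcomes, and treatment-by-centre heterogeneity.

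**1. Robust Wald test, equal centres.** The sandwich estimates the variance from five centre contributions with divisor K instead of K − 1, so z = t₄ × √(5/4). Rejection at |z| > 1.96 means |t₄| > 1.96 × √(4/5) = 1.753, and P(|t₄| > 1.753) = 0.154. Type I error is 15.4%. Equivalently, a correct 95% interval would be (2.776/1.96) × √(5/4) = 1.58 times as wide.

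**2. Score test with 1 df.** With centre scores u₁ to u₅ the statistic is T = (Σu)²/Σu², which cannot exceed K = 5. The smallest p is P(χ²₁ > 5) = 0.0253. In terms of t₄, T = 5t²/(t² + 4). T > 3.84 requires t² > 4 × 3.84/(5 − 3.84), that is |t₄| > 3.64, which has probability 0.022. The true size is 2.2%, so the test is conservative.

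**3. Power of that score test, one outcome, equal centres.** At 0.28 SD the noncentrality is 0.28/√(2/320) = 3.54. A noncentral t₄ with that value exceeds 3.64 with probability 0.54.

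**4. Simulation** (640 completers; ICC 0 to 0.05)

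| Setting, null hypothesis | Robust Wald | 1-df score |
|---|---|---|
| Equal centres, 128 each | 14.9-15.9% | 1.9-2.4% |
| Unequal, 110/80/60/40/30 per arm | 17.5% | 1.6% |
| Unequal, 320/120/80/60/60 in total | 17.8-21.4% | 1.3-2.1% |

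Comparators under the null:

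- Participant as cluster, three outcomes: 4.5-4.9%. With centre fixed effects added: 5.0% for equal centres and 5.4% for 110/80/60/40/30 per arm.
- Centre-exchangeable GEE with model-based standard errors, one outcome: 4.3-5.4% without treatment-by-centre heterogeneity, and 8.6-11.4% if that heterogeneity has SD 0.1.
- Model-based standard errors, three stacked outcomes: about 7.7%.

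| Power at 0.28 SD | Centre-cluster score | Comparator |
|---|---|---|
| One outcome, equal centres | 54% | 93% (model-based) |
| Three outcomes, equal centres | 88-91% | about 100% (participant clusters) |
| Three outcomes, 110/80/60/40/30 per arm | 50% | about 100% (participant clusters) |

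The 15.4%, 2.2% and 0.0253 in steps 1 and 2 follow from five equal clusters and the uncorrected sandwich alone. The unequal-centre and three-outcome rows depend on the further assumptions.

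**The case against.** The strongest reply is that section 5.2.1 does not state the conditions under which these figures arise.

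- **Scope.** The centre sentence follows the one on secondary outcomes. If the primary model clusters the three outcomes within participant, the bound of 5 does not touch the primary score test. This stands. The sentence refers to the analysis without restriction, so the wider reading is possible but not established.
- **Variance estimator.** None is named, and neither is a Wald test. Such detail may sit in an analysis plan that is not shown. This stands, and it makes the error rates conditional. It does not clear the rule, because model-based errors hold the level only for a single outcome without treatment-by-centre heterogeneity.
- **Role of the score test.** It could be read as a check that one common effect fits all three outcomes. The 1-df power figures would not describe such a check. A 2-df version on five clusters would have a smallest p of 0.082 and could never reject at 0.05, so centre clustering would harm that use too.
- **Other analysis.** The section also lists a general linear model for continuous outcomes, which would work at participant level. It does not say which result takes precedence over the GEE.

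A reader might infer that the planned primary test cannot reach significance. The documents do not support this: the threshold is 0.05, not 0.025, and a smallest p of 0.025 leaves room to reject. A reader might also infer that most of the power is lost. That would rest on an effect such as 0.15 SD (37% for equal centres against 81-82% with participant clusters), which the protocol does not use. At its own 0.26-0.31 SD the loss on three outcomes with equal centres is modest.

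**Conclusion.** The concern holds in conditional form. The stated within-centre correlation makes five hospitals the GEE clusters, at least for the continuous secondary outcomes and possibly for the primary model. With the uncorrected sandwich variance, Wald tests reject a true null about 15% of the time with equal centres, and about 17-21% with the unequal sizes assumed here. The 1-df score test errs the other way, with size about 2% and reduced power.

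It would go too far to call the planned inference invalid without condition, since the variance estimator and the reach of the centre sentence are both left open. What does not depend on either is that the primary model needs the participant as its cluster, and that a centre-level exchangeable structure does not provide this. The point should be fixed, and before unblinded analysis, because a later choice of cluster or variance could change which results are significant.

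**What to change.** In section 5.2.1, delete the exchangeable within-centre correlation and replace the sentence with:

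> Centre, the randomisation stratum, enters every primary and secondary model as a fixed effect (four indicators); the participant is the clustering unit for the three stacked primary outcomes.

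The cost is 5 − 1 = 4 degrees of freedom out of about 640 completers, and a change of wording. No data collection or sample size is affected. Inference then refers to the five participating hospitals.

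If the centre is kept as the cluster for some reason, the plan should name the models it applies to, the variance estimator and a small-sample correction. That is the weaker option, because it still rests the analysis on five units when the randomisation does not require it.

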## **6. Quality control**

The proposed trial will comply with China's Standard for Quality Management of Clinical Trials (GCP) and other relevant laws and regulations on clinical trials. Participants' personal information will be confidential and will not be disclosed without permission.

The standard quality control process will be carried out at each step of the study, including repeated laboratory measurements in 5-10% of random blind samples, and all data will be entered independently.

Establish a research procedure manual (MOP): we will develop a standardized process of data collection, which will include the recruitment of subjects, instructions for the use of tables, intervention programs, index measurement, specimen collection and management, etc., to guide all tabular information entry and diagnosis and treatment processes, and other aspects of the study.

Training: all researchers will receive relevant training before the start of the study, including standardized processes, recruitment processes, follow-up, intervention programs, measurement procedures, and the use of MOP. At the same time, regular retraining sessions will be conducted to ensure the quality of research.

Quality monitoring and reporting: quality control personnel will regularly review the QC data, including the timeliness of the completion of the visit, data collection, program implementation and data quality.

A steering committee (SC), chaired by [name], Nanfang Hospital, Southern Medical University, is responsible for the study. The SC is responsible for organizing and supervising the research implementation, approving the research program, including significant revisions, monitoring subject recruitment and retention,

delivering of intervention programs, data collection, quality control, and respond to questions raised by the institutional review board (IRB). The research center will play a critical role in the patient recruitment, randomization, delivery of intervention, data collection, quality control, data analysis, and the report and publication of the research results.

In order to facilitate communication among investigators and research staff, regular working meetings will be held. The SC will discuss and make decisions on relevant scientific and management issues in the study with three live meetings a year and monthly conference calls. Important information, such as recruitment yields, data completion and quality, and adherence to the protocol, will be sent to committee members and core staff by e-mail monthly.

## **7. Ethics Approval**

The proposed trial complies with the Helsinki Declaration (1996 edition) and the relevant regulations of Chinese clinical trials. The study protocol and informed consent form are approved by institutional review boards of the Nanfang Hospital of Southern Medical University before implementation.

All revisions on protocol or informed consent (excluding administrative changes and revisions that have no impact on the participants, implementation of trial, or data) must be submitted to the Ethics Committee for approval prior to the implementation of amendments. Serious adverse events must be reported to the Ethics Committee as required by the ethics committee.

Before enrollment, the informed consent is accessible to the patients. The background, aim, methods and measurements of the trial are introduced thoroughly by the researcher. Individual rights and obligations, possible risks and benefits during the intervention must be explained in detail. Researchers are responsible to answer questions raised by patients accurately in plain language. Patients are allowed to discuss with family members and decide whether to participate in the study. All subjects approve the collection and use of the trial data and are willing to participate the follow-up. Researchers should obtain the permission of the participants to use the collected data if they withdraw. Participants will be required to sign informed consent before enrollment. Informed consent will be kept as original materials for future reference. The study will be registered on the NIH

60 Clinical Trial website before enrollment.

61 **8. Proposed study timeline**

62 The implementation of the trial is expected to take about 2.5 years after registration in the clinicaltrials.gov  
63 the trial, in which MOP development, personnel training, and subject recruitment take about 1 year.  
64 Intervention and data collection take about 1 year, data entry, data analysis and manuscript preparing take about  
65 0.5 years.

66

